### 2.7 Subject withdrawal

A subject must be withdrawn from the study if he/she withdraws consent. Subjects who 1) experience adverse events, or 2) have pre-existing violation of entry criteria may remain in the study unless the investigator determines that it is not in the subject’s best interest to continue. The specific reason for withdrawal should be indicated.

Subjects who have withdrawn from the study will be invited to follow up at the last study visit, i.e., week 16 after the randomization visit to detect any delayed clinical events.

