## 2 Methods

### 2.1 Study design

This is a randomized, double-blind, placebo-controlled trial. A 2-week screening period will be implemented, and then eligible subjects with AR will receive either “Yupingfeng Powder with variation” granules or placebo granules for 8 weeks followed by a post treatment visits at weeks 12 and 16.

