## 3 Study outcomes

### 3.1 Primary outcomes

1. The change in the TNSS at week 8.

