## 5 Sample size and statistical methods

### 5.1 Sample size calculation

This study is mainly focused on determining the efficacy of “Yupingfeng Powder with variation” for AR patients. The primary outcome is the TNSS. With reference to data from a previous similar study (Chen, 2015), the sample size was calculated using two means with software G*Power. The mean of nasal score of the treatment group was 0.5 ± 0.1 and that of the control group was 3.6 ± 0.2. To obtain a significance level of 5%, a power of 80%, 52 subjects are required. Allowing for a 10% dropout rate, 58 subjects are needed, with 29 in each group.

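### Subjects removed from the study before week 8 who still consent to assessment have no planned route to the week-8 primary outcome

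*Protocol article*

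**What the plan says.** Protocol article, section 2.7, sets out who leaves the study and what happens next:

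- One ground for leaving is mandatory: "A subject must be withdrawn from the study if he/she withdraws consent".
- Subjects with adverse events or pre-existing entry violations "may remain in the study unless the investigator determines that it is not in the subject’s best interest to continue".
- Those who have left "will be invited to follow up at the last study visit, i.e., week 16 after the randomization visit", and the stated purpose is "to detect any delayed clinical events".

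The primary outcome in section 3.1 is "The change in the TNSS at week 8". Section 3.2 lists TNSS at weeks 4, 12 and 16 as secondary. Treatment runs "for 8 weeks followed by a post treatment visits at weeks 12 and 16" (section 2.1), so the primary time point is the end of treatment.

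Section 5.1 makes one provision for losses: "Allowing for a 10% dropout rate, 58 subjects are needed, with 29 in each group".

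**The concern.** The article gives a specific rule for contact after withdrawal, and the one contact it names falls 8 weeks after the primary time point. Followed as written, the rule leaves a subject removed at, say, week 3 or week 6 without a primary value, even if that subject would have been willing to score four nasal symptoms at week 8.

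The reason for leaving may be related to treatment or to outcome. Section 2.7 itself gives adverse events as a situation in which the investigator may decide that a subject should not continue. If leavers differ from those who stay, and differ more in one arm than in the other, the comparison of observed week-8 scores is biased. Inflating the sample size replaces the number lost but does not correct that bias.

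**Working it through.** **1. The passages side by side**

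| Subject | Week-8 TNSS under the text |
|---|---|
| Has an adverse event or entry violation, remains in the study | Yes, at the scheduled visit (2.7, Table 1) |
| Leaves between weeks 8 and 16 | Yes, already collected |
| Leaves before week 8, refuses all further contact | No, and no rule can change that |
| Leaves before week 8, would still agree to assessment | No; the only contact named is at week 16 |

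The concern applies to the last row only.

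**2. The plan's dropout step (5.1)**

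Inputs: 52 subjects before dropout, 10% dropout.

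- 52 / (1 − 0.10) = 57.8, rounded up to 58.
- Per arm: 26 / 0.9 = 28.9, rounded up to 29.

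This step reproduces. How the 52 was obtained is a separate matter and is not needed here.

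**3. How many subjects**

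0.10 × 58 = 5.8, about 6. Under the plan's assumption this is a ceiling. Section 5.1 gives neither the timing nor the reasons for dropout, so the share that leaves before week 8 and remains willing to be assessed is unknown.

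**4. Size of a possible bias**

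For one arm, let f be the fraction lost and g the mean improvement of those who stay minus the mean improvement of those who leave. The observed mean improvement then exceeds the whole-arm mean by f × g. The bias in the between-group difference is

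bias = f(active) × g(active) − f(placebo) × g(placebo).

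The documents give no value for g. Assume 2 to 3 TNSS points, with 29 per arm:

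| Losses | Bias in the difference (points) |
|---|---|
| 3 in each arm, same g | 0 |
| 3 active with this g; placebo leavers like placebo stayers | 3/29 × 2 to 3 = 0.21 to 0.31, in favour of active |
| 3 placebo with this g; active leavers like active stayers | 0.21 to 0.31, against active |
| All 6 in one arm (extreme) | 6/29 × 2 to 3 = 0.41 to 0.62, direction set by the arm |

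In SD units, if one arm loses 5% to 20% and leavers differ by 0.5 to 1.0 SD (assumed), that arm's mean shifts by 0.05 × 0.5 = 0.025 SD up to 0.20 × 1.0 = 0.20 SD.

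**5. Scale**

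With 26 per arm, two-sided 5% and 80% power, a t-test detects a standardised difference of about 0.79. The article does not state this figure; it follows from the 26. With an assumed SD of 2 to 3 points it equals 0.79 × 2 = 1.6 to 0.79 × 3 = 2.4 points. A one-sided loss of 3 is then between 0.21/2.4 = 9% and 0.31/1.6 = about 20% of that difference. The extreme case is between 0.41/2.4 = 17% and 0.62/1.6 = 39%.

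**The case against.** The strongest reply is that the week-16 contact is a safety contact and says so. It was never meant to retrieve efficacy data, and the sentence does not exclude other contacts. Section 2.7 lets subjects with adverse events stay, and they keep week 8. The one mandatory ground for leaving is withdrawn consent, which no collection rule can override. A condensed article may leave the detail of visits after treatment stops to a full protocol. Missing-data methods belong in an analysis plan, and a week-4 TNSS would exist for anyone who leaves after that visit.

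Most of this stands, and it narrows the point to subjects removed before week 8 who still consent. It does not remove it. The article does state a rule for withdrawn subjects, and that rule offers nothing at week 8. A week-4 score can support a model, but it is not the primary value, and no analysis plan can supply a measurement that was not taken.

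Three stronger readings are tempting, and the documents do not support them:

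- *The week-16 visit supplies a late TNSS in place of week 8.* Section 2.7 does not say that TNSS is taken from withdrawn subjects at that contact.
- *The plan treats stopping treatment and leaving the study as one event.* Section 2.7 speaks of the study throughout. Section 4.1 separately speaks of suspending treatment after a severe adverse reaction and does not call that withdrawal. The article is silent on whether assessments then continue, which is not the same as merging the two.
- *All of the roughly 6 dropouts are early and recoverable.* Section 5.1 gives no timing and no reasons.

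**Conclusion.** The point holds in limited form. Section 2.7 plans no week-8 TNSS for subjects who leave the study before week 8 but would still agree to be assessed. They are an unknown part of at most about 6 of 58 under the plan's own 10% assumption. Their loss may bias the primary comparison in either direction. On the assumed values the bias runs from nothing, when the arms lose similar people, through 0.2 to 0.3 points for a one-sided loss of 3, to 0.4 to 0.6 points in the extreme case. The gap of 2 to 3 points and the SD of 2 to 3 are assumptions, not figures from the article.

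A reader might infer that the primary analysis becomes a completers analysis and that the randomised comparison is lost. That goes too far. The article states neither an analysis set nor a missing-data rule, both may sit in a plan not shown, and on the plan's assumption about 90% of subjects are retained. Nor can it be said that the result would be too favourable to the active arm, since placebo leavers without benefit would push it the other way.

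The change is worth making because the gap is avoidable and cheap to close. It is not a fatal flaw.

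**What to change.** In section 2.7, add that subjects who stop study treatment or are removed before week 8, and who have not withdrawn consent to follow-up, are asked for the week-8 TNSS and are analysed in the arm to which they were randomised. The score can be taken at the scheduled visit, or by telephone or form, since section 3.3.1 makes it self-assessed. Keep the week-16 safety contact as it is. The change concerns data collection only and does not touch who stops treatment or why.

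The cost is a short amendment and contacts with at most about 6 people under the plan's assumption, at a visit that Table 1 already schedules. Section 9 reports 11 participants recruited at 18 July 2022, so at that date most week-8 assessments were still to come. The change will not recover subjects who refuse all contact, so it reduces the loss but does not end it.

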## 3 Study outcomes

### 3.1 Primary outcomes

1. The change in the TNSS at week 8.

### 3.2 Secondary outcomes

1. The change in the TNSS at weeks 4, 12, and 16.2. The changes in frequency of AR episodes and their severity VAS at weeks 4, 8, 12, and 16;3. The changes in the RQLQ score or PADQLQ score;4. The changes in the serum levels of total IgE and cytokines (IL-10 and IL-17) at weeks 8 and 12;5. The changes in the gut microbiota composition in stools at week 8; and6. Adverse events (graded by CTCAE) related to study treatment.

### 3.3 Study assessment

#### 3.3.1 Nasal symptom score

The TNSS will be self-assessed by subjects to evaluate four nasal symptoms (rhinorrhea, sneezing, nasal obstruction, and nasal itching), using a four-point scale as shown (Pfaar et al., 2014):
0=no symptoms

$$1=mild\;symptoms\;\left(sign/symptom\;clearly\;present,\;but\;minimal\;awareness;\;easily\;tolerated\right)$$

$$2=moderate\;symptoms\;\left(definite\;awareness\;of\;sign/symptom\;that\;is\;bothersome\;but\;tolerable\right)$$

$$3=severe\;symptoms\;\left(sign/symptom\;that\;is\;hard\;to\;tolerate;\;causes\;interference\;with\;activities\;of\;daily\;living\;and/or\;sleeping\right)$$

The higher the score, the more severity of the symptom.

#### 3.3.2 Visual analog scale (VAS)

The VAS ranges from 0 (nasal symptom free) to 10 (nasal symptom extremely bothersome) to assess the severity of nasal symptom disturbance and has been validated for use in the quantitative evaluation of AR severity (Bousquet et al., 2007). The higher the score, the more severity of the symptoms.

#### 3.3.3 Rhinoconjunctivitis quality of life questionnaire (RQLQ) for aged 13 and above

The RQLQ is a disease-specific questionnaire consists of 28 questions covering seven domains including activities, sleep, non-nose/eye symptoms, practical problems, nasal symptoms, eye symptoms and emotional problems, that can assess quality of life impairment in AR patients. This questionnaire (Juniper and H Guyatt, 1991).

#### 3.3.4 Paediatric allergic disease quality of life questionnaire (PADQLQ) for aged 5–12

The PADQLQ is a questionnaire designed for children answering without the parental help. It consists of 26 questions with three domains: activities (eight questions), symptoms (15 questions), and emotions (three questions). For each question, the subjects are asked for the perceived bother due to their allergic diseases. A 6-point scale from “not bothered” (score = 0) to “extremely bothered” (score = 6) is used to recording the perceived degree of bother. The total score of the PADQLQ is derived by summation of the scores for all 26 questions. The score for each of the domains is also calculated by summation of the relevant scores (Ng et al., 2011).

#### 3.3.5 Serum levels of cytokines and IgE

Blood samples will be taken to detect the serum level of cytokines IL-10 and IL-17 and specific IgE using enzyme-linked immunosorbent assays (ELISAs). These are the markers for inflammatory response. The higher the value, the more severity of the symptoms.

#### 3.3.6 Composition of gut microbiota

Stool samples will be collected to detect bacterial taxa present by using ribosomal ribonucleic acid (rRNA) sequencing to observe the influence of Chinese medicines on the composition of the gut microbiota. This experiment is exploratory in nature and no specific microbiota is known.

## 4 Possible risk and adverse event reporting

### 4.1 Possible risks and discomfort

There is minimal discomfort in blood taking. No serious adverse event has ever been reported but only mild discomfort of taking Yupingfeng Powder, including feeling of abdominal distension or increase in acne (Chan and Chien, 2014). The adverse reaction will be recorded and the treatment will be suspended when severe adverse reaction occurs. Un-blinding may also be done if necessary when severe adverse events occur.

### 4.2 Adverse events

An adverse event is any undesirable medical event occurring in the subject within the trial period, whether or not it is related to the study intervention. The assessment of adverse event will be recorded according to CTCAE 4.0 which is a standard assessment tool.

### 4.3 Serious adverse events

A serious adverse event is an adverse event that results in one of the following outcomes:• Death• Life-threatening• In-patient hospitalization or prolongation of existing hospitalization• A persistent or significant disability or incapacity• A congenital anomaly or birth defect

The definitions of causal relationship to study intervention are the same as those for adverse events. A standard serious adverse event form will be used (provided by The Chinese University of Hong Kong—New Territories East Cluster Combined Research Ethics Committee [Joint CUHK-NTEC CREC] at http://intranet.ccter.cuhk.edu.hk/sae/) to report the events within 24 h after acknowledgement.

## 5 Sample size and statistical methods

### 5.1 Sample size calculation

This study is mainly focused on determining the efficacy of “Yupingfeng Powder with variation” for AR patients. The primary outcome is the TNSS. With reference to data from a previous similar study (Chen, 2015), the sample size was calculated using two means with software G*Power. The mean of nasal score of the treatment group was 0.5 ± 0.1 and that of the control group was 3.6 ± 0.2. To obtain a significance level of 5%, a power of 80%, 52 subjects are required. Allowing for a 10% dropout rate, 58 subjects are needed, with 29 in each group.

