### 5.2 Statistical analysis

Baseline data (gender, age, vital signs) will be descriptively summarized. Differences of measurement data between the groups will be assessed using *t*-test for normally distributed continuous variables and Wilcoxon signed rank test for non-normally distributed variables.

Measurement data of different groups in each visit will be reported as mean ± standard deviation (SD). Intra-group comparisons between baseline and each visit will be conducted by using paired *t*-test (or Wilcoxon signed rank test). Comparisons between groups will be conducted by using an analysis of variance (ANOVA), with other confounding factors like multicenter character conducting the covariate analysis. Statistical analysis for the data which do not meet above conditions (e.g., non-normal) will be conducted with the use of non-parametric test.

For AEs analysis, comparisons of the incidence rate of AEs between groups will be conducted with the use of χ^2^ test. The investigators need to list and describe the AEs occurred in this trial. If the data do not conform to χ^2^ test (data include 0, or theoretical frequency is below 5), Fisher’s exact test will be used.

For laboratory parameters, Spearman’s coefficient correlation will be used for comparison with different parameters and one way ANOVA test for significant correlation between groups.

All *p* values and 95% confidence intervals are two-sided, and *p* < 0.05 is considered statistically significant. Statistical analyses will be carried out exclusively by an independent statistician. All analyses will be performed by using SPSS, version 24 (SPSS).

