## 8 Discussion

AR is a common disease (Dykewicz and Hamilos, 2010) that may affect the quality of life, sleep and work performance of the patients (Dykewicz and Hamilos, 2010). However, current available treatments for AR mainly include steroids and antihistamine (Ni, 2011), and the therapeutic effects are not always desirable (Peng, 2014; Chen, 2015). For this reason, many AR patients often seek help from Chinese herbal medicine, which has been shown to be effective in managing the patients’ symptoms. Chinese herbal medicine poses to be a valuable alternative for AR (Luo et al., 2019).

Yupingfeng Powder is a well-known formula in TCM with a long history, and is commonly used to treat allergic disease (Chan and Chien, 2014; Yen et al., 2015). The results from a few clinical trials showed that Yupingfeng Powder on top of conventional medicine brought about high efficacy than conventional medicine alone in treating AR (Zhou and Lu, 2010; Ni, 2011; Peng, 2014; Chen, 2015). However, the clinical study on the efficacy and safety of Yupingfeng Powder alone in treating AR is few and far between. The proposed project aims to determine whether Yupingfeng Powder is effective and safe in managing AR.

It should be noted that in this trial we have modified the original formula of Yupingfeng Powder. The original formula was designed to improve the immunity and tonifying the Lung and Spleen Qi. In this study, several additional herbal medicines are added to the formula to strengthen the functions of the original formula. For example, *M. biondii* (Xin-Yi-Hua), processed *X. strumarium* (Chao-Cang-Er-Zi) and *P. grandiflorus* (Ji-Geng) are added to relieve the nasal congestion of AR, while Processed Dragons bones (Duan-Long-Gu), processed *O. concha* (Duan-Mu-Li), *D. dasycarpus* (Bai-Xian-Pi) and *T. chebula* (He-Zi) have the ability to reduce sneeze and nasal discharge often seen in AR patients. *G. lucidum* (Chi-Ling-Zhi) and Cordyceps sinesis powder (Chong-Cao-Jun-Si-Fen) are used to increase the overall immunity of the body, while *G. littoralis* (Bei-Sha-Shen) enhances the Lung qi tonifying effect of the original formula. The modified formula is specifically designed for AR, and therefore is expected to produce better efficacy on the treatment of AR.

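### The 52 subjects in section 5.1 do not follow from the means and spreads given as their basis, and the assumption behind 80% power is not stated

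*Protocol article*

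**What the plan says.** Section 5.1 (Sample size calculation) names the endpoint, "The primary outcome is the TNSS", and the method: "the sample size was calculated using two means with software G*Power". The inputs are credited to an earlier study that the article calls similar: "The mean of nasal score of the treatment group was 0.5 ± 0.1 and that of the control group was 3.6 ± 0.2". The result follows directly: "To obtain a significance level of 5%, a power of 80%, 52 subjects are required". A 10% dropout allowance then raises this to 58, or 29 per group.

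Other sections supply the rest. Section 2.5 sets 1:1 allocation. Section 3.1 defines the primary outcome as the change in TNSS at week 8. Section 5.2 makes p values and confidence intervals two-sided and uses mean ± SD as the trial's own reporting format. Section 5.1 does not label its ± values. The article gives no other effect size, SD or target difference.

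**The concern.** The section sets out a full chain of method, inputs, significance level, power and result, so it can be checked. A gap of 3.1 points with spreads of 0.1 and 0.2 means two distributions that hardly overlap, and a two-means calculation on such data cannot call for 26 subjects per arm.

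What is at stake is the meaning of the 80% power claim for the primary outcome. As printed, it tells the reader that the trial was sized on a 3.1-point difference with very small variability. If 52 came from some other assumption, the reader does not know what difference the trial can reliably detect, and so cannot judge what a non-significant week-8 result would leave open.

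**Working it through.** **Inputs.** Means 0.5 and 3.6, spreads 0.1 and 0.2, 5% significance, 80% power (section 5.1); 1:1 allocation (section 2.5); two-sided testing (section 5.2, not repeated in 5.1).

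**1. The stated inputs, with ± as SD.**
- Difference: 3.6 − 0.5 = 3.1
- Pooled SD: √((0.1² + 0.2²)/2) = √0.025 = 0.158
- Standardised difference: d = 3.1/0.158 = 19.6
- Normal approximation: n per group = 2(1.96 + 0.84)²/d² = 15.7/384 = 0.04, which rounds up to 1
- Noncentral t: 2 per group, the smallest number that allows a two-sample t-test, with power above 99.9%

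The stated inputs thus give 4 subjects in total, not 52. At 26 per group they give power of about 100%, not 80%. Using an SD of 0.1 or 0.2 for both arms, testing one-sided, or raising power to 90%, 95% or 99% still gives 2 per group.

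**2. With ± as a standard error.** The SD is then 0.158 × √m, where m is the number per arm in the source study. The article does not give m, so these values are assumptions.

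| m per arm (assumed) | SD | d | n per group |
|---|---|---|---|
| 20 | 0.71 | 4.38 | 3 |
| 50 | 1.12 | 2.77 | 4 |
| 100 | 1.58 | 1.96 | 6 |
| 600 | 3.87 | 0.80 | 26 |

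Only a source study of about 600 per arm would give 26 per group.

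**3. With 52 as a per-group figure.** Section 5.1 excludes this, because it goes on to 58 in total with 29 per group.

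**4. The dropout step.** 52/0.9 = 57.8, which rounds up to 58, or 29 per group. This reproduces. The fault lies only in the step from the inputs to 52.

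**5. What 26 per group corresponds to (noncentral t).**
- Two-sided 5%, 80% power: d = 0.79. With a 3.1-point difference this needs an SD of 3.1/0.792 = 3.9, about 25 times 0.158.
- Two-sided d = 0.8 gives 26 per group, 52 in total (power 80.7%).
- One-sided d = 0.7 also gives 26 per group, 52 in total (power 80.1%).

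Neither d = 0.8 nor d = 0.7 appears in the article.

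**6. In TNSS points.** The article gives no SD for TNSS change. For assumed SDs of 2, 3 and 4, the difference detectable with 80% power (two-sided) is 0.792 × 2 = 1.6, 0.792 × 3 = 2.4 and 0.792 × 4 = 3.2 points. Four symptoms each scored 0 to 3 (section 3.3.1) give a maximum total of 12.

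**The case against.** The strongest reply is that nothing here harms the trial. On the stated inputs 52 is far more than enough, the dropout step is right, and the test, the significance level and the enrolment are unaffected. A journal article also condenses a longer protocol, which may hold the real G*Power input. Most of this stands, and it limits the point. It does not remove it, because the article does more than leave an input out: it attributes 52 to specific figures that do not produce it.

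A reader might infer three stronger things that the document does not support.

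- *The trial is underpowered.* No shortfall is shown. Whether 58 is adequate depends on a justified difference and SD for TNSS change, and the article gives neither.
- *The trial was in fact sized for 0.8 SD.* Two-sided d = 0.8 reproduces 52 exactly, but so does one-sided d = 0.7. Section 5.1 states no sidedness, and the two-sided statement in section 5.2 concerns the analysis.
- *The source study was an add-on trial.* Section 8 cites it with three others for the summary that "Yupingfeng Powder on top of conventional medicine brought about high efficacy than conventional medicine alone in treating AR". A grouped citation raises the question but does not settle that study's design.

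It might also be held against the calculation that the inputs are group mean scores while the primary outcome is a change. Under randomisation the expected between-group difference is the same for both. Only the SD differs, so this is a reason to state the SD of change and not a separate error.

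**Conclusion.** The point holds as a failure of the printed calculation. The stated inputs give 2 per group with ± as SD, or 3 to 6 per group with ± as a standard error from arms of 20 to 100 (assumed), against 26 per group stated. No sidedness, SD or power variant tried recovers 52, and the standard-error reading does so only at about 600 per source arm. The assumption behind 80% power is therefore not stated, and how 52 was obtained is unknown.

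It should be corrected because it is the only justification given for the sample size on the primary outcome. The figure of 0.79 SD assumes 26 evaluable per group and a two-sided 5% t-test. It describes what the planned number can detect and does not reconstruct the sponsor's reasoning. The conversions to points rest on assumed SDs.

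**What to change.** 1. Remove 0.5 ± 0.1 versus 3.6 ± 0.2 as the basis for 52.
2. State the effect size and the SD of week-8 TNSS change that were actually entered in G*Power, and whether the calculation was one- or two-sided.
3. If these cannot be recovered, keep 58 and say what it can detect. Suggested wording: *With 26 evaluable subjects per group, the trial has 80% power at a two-sided 5% level for a standardised difference of 0.79 in the change in TNSS at week 8; assuming an SD of [value], this is a difference of [value] points.* The points are 1.6, 2.4 or 3.2 for SDs of 2, 3 or 4. The SD chosen should be labelled as an assumption and given a source.
4. As a secondary matter, confirm the design of the cited study and say that its contrast may differ from this trial's comparison with placebo.

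Restating the basis at 58 costs wording only and adds no patients. The stated basis becomes less favourable than the printed one. Section 9 reports 11 participants recruited by 18 July 2022.
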